**Parasitological examination**

- A thumb sized fresh stool specimens will be collected on the spot from all the study subjects.
- Children will be provided with:
  - clean labelled plastic screw-top containers (for sample collection)
  - plastics sheet (to catch the stool in the toilet)
  - applicator stick (to transfer the sample).

Stool analysis will be done using:

- Direct saline wet mount
  - Formalin ethyl-acetate concentration technique
  - Kato-Katz technique (thick smear 41.7mg)
- Duplicate slides will be prepared for each stool specimen and for each of the techniques used.
- 10% of randomly selected stool smears will be re-examined for each sample collected for quality control purposes.

**Sociodemographic data collection**

Two separate structured questionnaires (child and household) will be prepared and administered in a local language during recruitment to generate information on the demographic and personal hygiene and sanitation behaviours.

**Concealment and blinding**

Children and household assignment sequence will be concealed. Researchers assessing the outcomes will be blinded to group assignments. Lab personnel will be blinded to group assignment and to the assessment outcomes. Participating children and their families can be aware of the intervention they receive but will be blinded for the study hypothesis and the intervention(s) given to the other groups. The study will be explained as an assessment of intestinal parasitosis, anaemia and malnutrition among school-aged children, while the principal purpose of assessing the impact of hand washing and nail clipping will be concealed.

[figure not shown]

**Specific Aim I: Evaluate the impact of hand washing with soap and hand nail clipping on parasite re-infection rates, intensity and self-reported illness.**

**Objective and Rationale:** Effective preventive tools serve in decreasing the burden of entroparasite infections. Periodic drug administration, proper hygiene and sanitation are known to keep the levels of infection below those associated with morbidity, and hence improve the health and development of individuals, especially of children. The fact that parasitic infections impair children's growth and development is of a public health concern.

Although treatment reduces both transmission and infection rates of intestinal parasitic infections, whether this intervention measure is sustainable solution is not clear as rapid re-infection usually occurs. There is also emerging evidence that concurrent worm infections may have impacts on child development and nutritional status. The potential impacts of hand hygiene promotion activities on intestinal parasitosis and illness among children merit extensive investigation.

**Methodology:** Parasitological analysis will be carried out and children diagnosed positive for intestinal parasitic infections will be treated and recruited for the study. A detailed household listing and identification of households with children under investigation will be carried out. Upcoming allocation sequence will be concealed from participants and field workers, and households will be randomized to receive either: (a) hand washing with soap; or (b) hand nail clipping; or (c) both interventions; or (d) neither of the intervention packages. Children assigned to intervention arms of hand washing with soap and finger nail clipping will be provided with soap and nail clippers, respectively.

Fieldworkers will be trained on approaches to promote hand washing and hand nail clipping, standard procedure of hand washing with soap, data collection and reporting. Fieldworkers will visit households on a weekly basis throughout the study period to encourage hand washing, nail clipping and to record incidence of clinical symptoms. Same regular visits will be made to the control households. Sociodemographic data will be collected prior to the initiation of the study using structured questionnaire.

**Data collection and processing:** A series of parasitological screening activities will be done after completion each treatment phase based on the life cycle of each identified parasite species until parasite positive children are screened negative. Children who received hand washing with soap will be compared with children who received no hand washing and children under nail clipping intervention will be compared against the non clipping group. Differences of impact in different subgroups and possible interactions between the different intervention activities (hand washing with soap and nail clipping) will be analysed.

The aim of the study and procedures employed will be discussed with the local administrative leaders and health authorities, and with parents and children participating in the study.

Quality of the tests and accuracy of egg counts of each parasitological analysis period will be assessed by screening a random sample of 10% of the slides for a second time by a well-experienced laboratory technologists.

**Anticipated results:** The primary outcome measures will be:

- the proportion of children with reduced intestinal parasitosis re-infection rates in the intervention and control arm
- the proportion of children with reduced parasite load (infection intensity) rates in the intervention and control arms

The secondary outcomes will be:

- the proportion of children with reduced prevalence of anemia in the intervention and control arms

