### Requirement of parasite free children

Prior to random allocation to the intervention and control arms and following acquisition signed informed consent, children will be screened for intestinal parasitosis. Children screened positive for intestinal parasitic infections will be treated using standard treatment regimen. Parasite negative children in the respective households will be randomly assigned into different intervention and control groups and randomisation will be by sealed envelope method.

[figure not shown]

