### **Sample collection and Analysis following 6 months intervention**

#### **Parasitological examination**

- Following 6 months intervention children will be made to come to the schools where the laboratory will be established.
- A thumb sized fresh stool specimens will be collected on the spot from all the study subjects.
- Children will be provided with:
  - clean labelled plastic screw-top containers (for sample collection)
  - plastic sheet (to catch the stool in the toilet)
  - applicator stick (to transfer the sample).

Stool analysis will be done using:

- Direct saline wet mount
  - Formalin ethyl-acetate concentration technique
  - Kato-Katz technique (thick smear 41.7mg)
- Duplicate slides will be prepared for each stool specimen and for each of the techniques used.
- A child will be classified as re-infected if an infection was detected by any methods used.
  - 10% of randomly selected stool smears will be re-examined for each sample collected for quality control purposes.

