## **Data Processing and Analysis**

Data will be entered and processed on an appropriate software and will be analysed using appropriate statistical analysis methods. Effectiveness of interventions will be assessed using regression models by odds ratio with help of SPSS version 16 software. Effectiveness of an intervention will be estimated based on a comparison of all individuals allocated to receive a particular intervention package versus those allocated not to receive the intervention. Infection intensity differences between intervention and control arms will be analysed by arithmetic mean differences for the egg counts using the independent-samples t-test. Participants will be analysed according to the group to which they were randomized. Base-line demographic and hygiene information will be obtained using structured questionnaire. Questionnaires will be coded by investigator and statistician, and data entry will be done using an appropriate statistical software. Statistical significance will be tested with  $\chi^2$  and shall be set at  $p < 0.05$ .

**Problems and pitfalls:** The study is expected to have limitations arising from the study design to be followed, the process of data collection and nature of the study respondents. As behavioural trials are difficult to be blinded, systematic error is expected to occur due to the lack of blinding. An attempt to reduce this effect will be made by masking field workers to the identity of the assigned interventions and the outcome of interest. Field workers will check the presence of soap for hand-washing in the households other than those assigned to hand-washing intervention, and nail clippers in households other than assigned to the intervention during their weekly visits in an attempt to check for contamination.

Loss-to-follow-up will be reduced, and compliance during follow-up will be enhanced by recruiting children and households who are interested and reliable in to the selection process, and by arranging frequent contacts with individual members of the families.

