## **9. Inclusion and exclusion criteria**

### **Inclusion**

- children who are able to bring signed written informed consent
- children / households who agree to participate throughout the study period
- children who permanently live in the area and who are going to stay in the household throughout the study period
- children aged 6 to 15

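### The protocol gives two entry rules on infection status, and its 're-infected' outcome does not fit children who were negative at first screening

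*Protocol*

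**What the plan says.** The protocol describes entry in several places.

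- **Requirement of parasite free children:** children are screened before allocation. "Children screened positive for intestinal parasitic infections will be treated using standard treatment regimen", and then "Parasite negative children in the respective households will be randomly assigned into different intervention and control groups".
- **Specific Aim I, Methodology:** "children diagnosed positive for intestinal parasitic infections will be treated and recruited for the study". Children negative at first screening are not mentioned.
- **Specific Aim I, Data collection and processing:** screening is repeated after each treatment phase "until parasite positive children are screened negative".
- **Inclusion and exclusion criteria:** these cover consent, agreement to take part, residence, age ("children aged 6 to 15") and certain health conditions. Infection status does not appear.
- **Sample collection and Analysis following 6 months intervention:** "A child will be classified as re-infected if an infection was detected by any methods used". Status before the trial plays no part in this rule.
- **Sample size determination:** 216 households fill the four factorial cells at 54 each. The only allowance is for loss to follow-up.

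**The concern.** Who may be randomised and what the primary outcome means are matters for the protocol itself, and here the text supports two answers. A field team following the Specific Aim I sentence could enrol only treated, initially positive children. A team following the parasite-free section could enrol every child who is negative at allocation. Both could claim to have kept to the protocol.

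Each reading causes a difficulty. If initially negative children enter, a first detected infection is reported as a re-infection, and the result is attached to a population that its name does not describe. If only initially positive children enter, the outcome name is right, but 216 sampled households no longer yield the planned numbers because nothing was added for children screened out.

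**Working it through.** **Inputs, all from Sample size determination unless stated:** prevalence 72.2%; reduction 20%; power 80%; significance level 0.05; 90 per arm; 20% loss to follow-up; 216 households, so 108 per main-effect arm.

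**1. The protocol's own figure.** The stated formula with p1 = 0.722, p2 = 0.522 (20 percentage points) and a two-sided test gives

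n = (0.722 × 0.278 + 0.522 × 0.478) / 0.2² × (1.960 + 0.842)² = 0.4502 / 0.04 × 7.849 = 88.3.

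This reproduces the stated 88, rounded to 90. The total follows as 180 + 36 = 216. No term allows for children lost at screening.

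**2. Yield under each entry rule, one child per household.**

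| | Children from 216 households |
|---|---|
| Initially positive | 216 × 0.722 = 156 |
| Initially negative | 216 × 0.278 = 60 |

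- Every child negative at allocation enters: about 216 children, of whom about 28% were negative at first screening. Any infection in these children would be called a re-infection.
- Only initially positive children enter: about 156 children, or 78 per main-effect arm. Reaching 216 needs 216 / 0.722 = about 299 households.

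**3. Effect of two children per household.** The design section takes two children where a household has more than one eligible child. If every household supplied two and infection were independent between them (an assumption), the chance of at least one positive child would be 1 − 0.278² = 0.923. Then 216 / 0.923 = about 234 households would be needed. The range is therefore about 234 to 299. Clustering of infection within households would move the lower end up.

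**4. Power if 216 households are screened and only positives enter.** With the pooled two-sided formula, 72.2% against 52.2%, and mean proportion 0.622:

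power = Φ[(0.2 × √n − 1.960 × √(2 × 0.622 × 0.378)) / √0.4502].

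- n = 78: (1.766 − 1.344) / 0.671 = 0.63, so power is about 73.5%.
- n = 108: about 86.3%.
- After 20% loss (78 × 0.8 = 62.4 and 108 × 0.8 = 86.4): about 63.7% and 77.9%.

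These figures hold the protocol's two rates fixed. It gives no separate six-month risk for initially positive children.

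**5. What a baseline covariate could add.** The protocol gives no six-month risk by initial status, so a difference D between the two groups has to be assumed, with the same 20-point effect in each. The share of outcome variance explained is 2 × 0.722 × 0.278 × D² / 0.4502.

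| D | Variance explained | n per arm |
|---|---|---|
| 0 | 0% | 88.3 |
| 10 points | 0.9% | 87.6 |
| 20 points | 3.6% | 85.2 |
| 30 points | 8.0% | 81.3 |

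**The case against.** The best defence is that the passages can be read together. The Specific Aim I sentence does not say that only positives are recruited. Households are drawn from the census without regard to infection, the criteria are silent on it, and the parasite-free section gives the operational sequence: screen, treat, randomise those who are negative. On that reading, cleared positives and initial negatives both enter. A figure follows that section and is not shown, and it may settle the point. This inclusive reading is plausible and fits the design and sample size sections. It does not rescue the outcome, though: under it, the re-infection label is wrong for about 28% of children. A third reading, that only initially negative children are randomised, conflicts with the repeated screening of treated children and with the term re-infection.

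The defence is also right that the 299 figure is an upper end, because it assumes one child per household and the exclusive reading.

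A reader might go further and infer that the analysis ignores baseline infection status and so loses precision. The documents do not support that. The analysis section says "Effectiveness of interventions will be assessed using regression models by odds ratio with help of SPSS version 16 software" and neither lists nor excludes covariates. Such a list may be in a statistical analysis plan that is not shown. Nothing in the protocol shows that initial status is strongly prognostic. In a logistic model, adjustment also changes the estimate to a conditional odds ratio and does not simply narrow its standard error.

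**Conclusion.** The inconsistency stands. The protocol states two entry rules, the eligibility criteria do not choose between them, and the outcome rule calls every six-month infection a re-infection.

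The size depends on the rule followed. If all children negative at allocation enter, about 60 of 216 are initially negative and the outcome is misnamed for them. If only initially positive children enter, either about 234 to 299 households must be screened, or about 78 per arm remain, with power of about 73.5% before dropout. These figures rest on the 72.2% prevalence applying at screening. The power and the upper screening figure also assume one child per household, and taking two children in some households would soften the loss.

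A reader might also infer that mixing the two groups biases the trial. It does not, because allocation follows screening. What changes is the population and the meaning of the outcome, not the validity of the comparison between arms.

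**What to change.** - Reconcile the parasite-free section, the Specific Aim I Methodology paragraph and the inclusion criteria to one entry rule. The design, sample size and parasite-free sections already fit randomising every eligible, consenting child who is parasite-negative at the last examination before allocation, treated or not. If the sponsor intends only initially positive children, the number of households to be screened must be raised and stated.
- Name the primary outcome infection at 6 months, which is what the classification rule measures.
- Report re-infection among initially positive children as a secondary result.
- Optionally, add infection status at first screening (yes/no) to the regression model. The gain is unknown: about 1% to 8% of n if risk differs by 10 to 30 points between the groups, and none if it does not.

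Under the inclusive rule the cost is a few sentences. The screening result is already collected before allocation, so no new data are needed.

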## **Hand washing with soap and nail clipping: effect on intestinal parasitic infection in school-aged children: a factorial randomised controlled trial**

The study design shall be a factorial randomised controlled trial, whereby different intervention packages will be randomised among households with children recruited for the survey.

A total of 216 households with at least one school-aged child (aged 6-15) will be randomly selected by systematic random sampling method. Selection of households will be made based on the DHSS (Demographic Health Surveillance Site) baseline census. Hand-washing with soap intervention will be implemented at household level, using selected child (aged 6-15) within the household as study unit. If there is more than one child in the age group per randomised household two children will be selected by simple lottery method and will be included in the trial. Reported age of a child will be cross-checked using school- records, baptism certificates, local calendars and birth certificates (if available).

Each intervention and control group will have a fixed number of participants, and will be subjected to only one of the study interventions. Children in each group will be followed-up for 6 months and parasitological and haemoglobin data will be collected following intervention. Different intervention packages shall be evaluated separately (the primary comparisons are the main effects), in combination and also against the control groups (groups with standard habits and practices).

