### **Sample size determination**

Using the formula for ‘comparison of proportion of successes’ and assuming equal groups; based on data collected previously in the study area on prevalence of intestinal parasitosis among the age-group (72.2% -data from previous prevalence study in the area) and assuming prevalence reduction of 20%; taking a power of 80% and assuming a significance level of 0.05; the sample size per group (intervention and control) will be 90 households.

$$n = \frac{\left\{ \begin{array}{c} \text{success x failure} \\ \text{on treatment A} \end{array} \right\} + \left\{ \begin{array}{c} \text{success x failure} \\ \text{on treatment B} \end{array} \right\}}{(\text{success on A} - \text{success on B})^2} \times \text{‘magic number’}$$

Sample size = 88 (90); 90 households in intervention and 90 household in the control arm (n=180). Considering 20% loss-to-follow up = 180 + 36 = 216 households.

|                             |     | Nail clipping (NC) |     |       |
|-----------------------------|-----|--------------------|-----|-------|
|                             |     | Yes                | No  | Total |
| Hand washing with soap (HW) | Yes | 54                 | 54  | 108   |
|                             | No  | 54                 | 54  | 108   |
|                             |     | 108                | 108 | 216   |

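### Two primary outcomes of equal standing and no rule for which one decides: each intervention gets two chances at p < 0.05

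*Protocol*

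**What the plan says.** - **Outcomes.** Under Specific Aim I, Anticipated results, the list that begins "The primary outcome measures will be" has two bullets: "the proportion of children with reduced intestinal parasitosis re-infection rates in the intervention and control arm" and "the proportion of children with reduced parasite load (infection intensity) rates in the intervention and control arms". Neither is ranked above the other. Anaemia is the only outcome listed as secondary.
- **Comparisons.** The opening design section states that "the primary comparisons are the main effects". Specific Aim I, Data collection and processing, gives the form of these: "Children who received hand washing with soap will be compared with children who received no hand washing", and likewise for nail clipping. So there are two primary comparisons, one per factor.
- **Tests.** Data Processing and Analysis assesses effectiveness through regression and odds ratios. It analyses infection intensity separately, by a t-test on arithmetic mean egg counts. Significance is to be tested with chi-square and "shall be set at" p < 0.05. The section gives no other threshold.
- **Sample size.** Sample size determination uses one comparison of proportions, based on "prevalence of intestinal parasitosis among the age-group (72.2% -data from previous prevalence study in the area) and assuming prevalence reduction of 20" per cent, with 80% power and a significance level of 0.05. Parasite load does not appear there.

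**The concern.** Naming the main effects as the primary comparisons settles which arms are compared. It does not settle which endpoint decides. As written, each factor has two primary tests, and the protocol does not say how they combine. That has two consequences.

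First, if significance on either outcome is read as success, the chance of a false claim for a factor is above the 5% used to size the trial.

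Second, the outcomes can disagree. A child counts as re-infected if any of the three stool methods detects an infection (Sample collection and Analysis following 6 months intervention), whereas intensity is a mean egg count. One may differ between arms while the other does not. The protocol does not say whether the intervention has then worked, so this document leaves room to decide after the results are known.

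**Working it through.** **1. The protocol's own figure.** Inputs from Sample size determination: 72.2% without intervention, a reduction of 20 (read as percentage points, giving 52.2%), 80% power, significance level 0.05. The 'magic number' for two-sided 0.05 and 80% power is (1.96 + 0.84)² ≈ 7.85.

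n = (0.722 × 0.278 + 0.522 × 0.478) / 0.20² × 7.85 = (0.2007 + 0.2495) / 0.04 × 7.85 = 88.4

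This matches the stated 88. With 0.025 per outcome the same formula needs 107.0 per group. The stated size therefore contains one test on prevalence at the full 0.05 and no allowance for a second primary outcome.

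**2. Count of primary tests per factor.** Two outcomes, one main effect each, gives two tests. The threshold is 0.05 for each, taking the single stated threshold to cover the t-test as well.

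**3. False-positive rate per factor if either outcome counts.** Treat the two test statistics as bivariate normal with correlation r under no effect:

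rate = 1 − P(|Z₁| ≤ 1.96 and |Z₂| ≤ 1.96)

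| r (assumed) | rate per factor |
|---|---|
| 0 | 1 − 0.95² = 9.75% |
| 0.3 | 9.5% |
| 0.5 | 9.1% |
| 0.7 | 8.4% |
| 0.8 | 7.8% |
| 0.9 | 7.0% |
| 1 | 5.0% |

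**4. Check by simulation.** These are null 2×2 trials with 45 per cell, a test on the re-infection proportion and a t-test on egg counts. The count distributions are assumed.
- Zero-inflated lognormal counts, re-infection 15 to 70%: 6.4 to 8.2% per factor.
- Zero-inflated overdispersed counts, re-infection 30% or 72.2%: 7.4 to 9.3% per factor, with test correlations of 0.23 to 0.77.
- A near-degenerate case with test correlation 0.98: 5.8%.

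The t-test can be conservative on skewed counts, which pulls some of these below the normal-theory values.

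**5. Across the two factors.** Even with one primary outcome, two independent factors each tested at 0.05 give 1 − 0.95² = 9.75% for at least one false claim. That comes from the factorial design. It is accepted here because hand washing and nail clipping are treated as separate questions.

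**The case against.** The strongest reply is that the protocol already points to re-infection as the leading outcome. Its effectiveness analysis is the odds ratio, its sample size rests on prevalence, and re-infection is the outcome for which it sets a classification rule. All of that is true, and it means the statement that either outcome can establish effectiveness is an inference from a missing success rule and is not written anywhere. But these are hints. The list of primary outcomes gives parasite load the same standing, and nothing subordinates it.

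The sentence that sets p < 0.05 refers literally to chi-square, so applying it to the t-test is a reading. It is the natural one, since no other threshold is given.

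A statistical analysis plan may exist and could set a testing order. Multiplicity procedures and exploratory labels are ordinary content for such a plan, and their absence here is no finding. What this protocol does fix is two equal primary outcomes beside a sample size for one.

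A reader might go further in two ways, and the documents support neither:
- **Pooling all four primary tests and comparing the result with 5%.** This uses the wrong comparator. With separate questions per factor, 9.75% over both factors remains after any fix to the outcomes.
- **Adding the package-versus-control, interaction and subgroup analyses to the primary error rate.** The design section says "Different intervention packages shall be evaluated separately (the primary comparisons are the main effects), in combination and also against the control groups". That wording makes only the main effects primary, so the other analyses do not belong in that rate.

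**Conclusion.** The point holds, per factor. The protocol fixes two unranked primary outcomes, each with its own test, and gives no rule for success, while the trial is sized for re-infection alone. If either outcome is allowed to decide, the false-positive rate for each intervention is about 6 to 10% instead of 5%.

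That range is conditional on the correlation between the outcomes and on the egg-count distribution, both assumed. It also treats observations as independent, although up to two children per household may be enrolled. If the outcomes were almost perfectly correlated, the excess would nearly vanish. The ambiguity when the two results disagree does not depend on any of these assumptions.

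**What to change.** - **Specific Aim I, Anticipated results:** name re-infection at 6 months as the single primary outcome for each factor. It is the only outcome that the sample size covers. Move parasite load to first secondary outcome.
- **Data Processing and Analysis:** state that hand washing and nail clipping are separate questions, each tested at two-sided 0.05 on re-infection. Test parasite load at 0.05 for a factor only if that factor's re-infection test is significant. Otherwise report it as an estimate with a confidence interval.

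Because the second test opens only after the first succeeds, each factor stays at 5% across both outcomes, and the re-infection test keeps its full 0.05. Splitting alpha instead, at 0.025 per outcome, would lower power for the planned difference at 90 per group from 79.5% to 70.4% (pooled-variance calculation).

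The cost is wording, with no extra children, visits or tests. The small downside is that parasite load alone can no longer establish effectiveness, a claim for which the trial was not sized.
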